## 2.4 METHOD OF RANDOMISATION

### Clusters

The unit of randomisation will be defined by criteria relevant to each setting.

In Nigeria, the unit of randomisation will be Local Government Areas (LGAs). Each has a Department of Health headed by a Medical Officer of Health. All villages and PHCs within the LGA will be included in that cluster.

For the pilot phase, we will include four LGAs.

For the definitive phase, we will include 10 (5 intervention and 5 control) clusters in the trial with a public and private sector referral facility in the Ogun area. The four pilot trial clusters will remain in their assigned groups.

In Mozambique, the unit of randomisation is the Administrative Post. All villages and PHCs within the unit of randomisation will be included in that cluster.

There will be no Pilot phase in Mozambique. For definitive phase, we will include 12 (6 intervention and 6 control) clusters in the trial with a public and private sector referral facility in the provinces of Maputo (3 de Fevereiro, Maluana/Maciana, Ilha Josina/Calanga, Magude) and Gaza (Xilembene, Chicumbane, Nhancutse, Chibuto, Macia, Chissano, Mazivila, Messano)..

In Pakistan, the unit of randomisation will be defined by their union council. The villages and PHCs within that union council will be included in the cluster. We will recruit in the catchment area of adjacent union councils of Hyderabad and Matiari, Sindh, Pakistan.

For the pilot phase, we will include four union councils.

For the definitive phase, we will include 20 (10 intervention and 10 control) clusters in the trial with a public and private sector referral facility in the area adjacent to Hyderabad and Matiari (the latter to give patients choice in terms of referral options beyond the rural health centres (RHCs)). The four pilot trial clusters will remain in their assigned groups.

In India, the unit of randomisation will be the PHC. All villages within the PHC catchment area will be included in that cluster.

For the pilot phase, we will include four PHCs.

For the definitive phase, we will include 12 (6 study and 6 control) clusters in the trial with a public and private sector referral facility in the area adjacent to Belgaum and Bagalkot. The four pilot trial clusters will remain in their assigned groups.

[figure not shown]

**Figure 10 Trial organisation by country and clusters** CHCP community health care provider

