## 2.10 MEASURING THE OUTCOME MEASURES AT FOLLOW UP

In total, 54 village and urban clusters will be identified and randomised in the four countries (Nigeria: 10; Mozambique: 12; Pakistan: 20; India: 12). Each cluster will contain a health unit or regional health centre which has provided the training base for the corresponding cHCPs. Subsequently, the 27 clusters chosen to receive the intervention will be analysed against 27 control clusters.

A **baseline household and facility survey** is being carried out within the context of the CLIP Feasibility Study in all trial clusters to assess their socioeconomic characteristics and baseline maternal, perinatal, and neonatal mortality rates. In all countries except India this will be performed based on retrospective information on pregnancies occurring in the previous year. In India, the baseline data will draw from the

existing prospective Maternal and Neonatal Health Registry (MNH Registry). In Nigeria, due to the large cluster populations we will perform baseline surveillance on a random sample of households while in all other countries all households will be surveyed. This addresses the human resource constraints identified in Nigeria during the CLIP Feasibility study.

Subsequent **cross-sectional surveys of all households** will be conducted at varying frequency depending on current registration and surveillance activities in the relevant country: quarterly (Pakistan), 6-monthly (Nigeria and Mozambique), while in India, household surveys will continue prospectively using the MNH Registry. Although the cHCPs will routinely record information on maternal/perinatal births and deaths, the cross-sectional surveys will be conducted by a separate team to collect data on births, deaths, and care-seeking behaviour in the preceding study epoch. In Nigeria, due to population sizes and human resource constraints the cross-sectional surveys will focus on collection of maternal/perinatal mortality and morbidity for all households and a random sample of these households will receive a more in-depth survey including questions around birth preparedness, care-seeking and pre-eclampsia knowledge. The cross-sectional surveys will be considered the gold standard for the Trial as they will be applied equally between control and intervention clusters.

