### **2. METHODS AND RESEARCH PLAN (PAKISTAN AND MOZAMBIQUE)**

#### **2.1 Research design:**

We propose to use cost-effectiveness analysis (CEA), in conjunction with qualitative analysis, alongside the trial to prospectively evaluate the economic impact of the CLIP Trial. Cost-effectiveness remains the design of choice in economic evaluations when any particular experimental intervention (non-standard) is proposed to have similar or better clinical outcomes at decreased or equal costs compared with the standard intervention. Specifically,

our CEA will be based on a societal perspective, accounting for both costs to families and the health care system. The CLIP Trial is being conducted in four countries, which have different health care delivery systems, healthcare financing, resource allocation interests, diversity of community beliefs surrounding PE/E, care seeking behaviours and treatment preferences. Therefore, the combined approach (CEA and qualitative) will help in designing the cost modeling, and will support interpretation of economic analysis for decision makers who are considering evidence of economic value along with the effectiveness of interventions.

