## **2.2 Research setting:**

The primary CLIP Trial is recruiting in four countries in two regions i.e., South Asian countries (Pakistan and India); and African countries (Nigeria and Mozambique). Given the budgetary limitations, the economic evaluation of the CLIP Trial will take place in two countries (i.e., Pakistan, and Mozambique) representing each of the two regions in the CLIP Trial. These sites are selected in consultation with lead organizations in each country, as well as through existing academic relationships. The experience of community-based maternal or perinatal health research and research infrastructure in the country was also taken into account when selecting study sites for the economic analysis of the CLIP Trial.

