## **2.5 Methods for collecting resource utilization and unit costs data**

The information about resources utilization and costs will be collected from primary and secondary data sources in the intervention and control clusters. The consistent approach will be followed to collect these data in the intervention and control clusters. (See Table 1)

**Table 1:** Methods of collecting resource utilization and cost estimations in the intervention and control clusters

| Types of data        | Intervention Clusters                                                                                                                                                                           | Control Clusters |
|----------------------|-------------------------------------------------------------------------------------------------------------------------------------------------------------------------------------------------|------------------|
| Resource utilization | The quarterly surveillance tools, as follows:
A. Pregnancy registration (Form 1)
B. Regular community surveillance (Form 2)
C. Health facility patient admission chart review (Form 3) |                  |
| Unit cost-estimation | Review of hospital budget for maternal health services (costing for bed charges, consultant fees, diagnostic services, nursing services etc.)                                                   |                  |
|                      | Review of district level cHCP program budget (costing for cHCP Salaries)                                                                                                                        |                  |
|                      | Review of site specific CLIP Trial budget (costing for intervention package)                                                                                                                    |                  |

**2.5.1 The quarterly surveillance tools:** The structured questionnaires will be administered during the quarterly CLIP Trial surveillance in all intervention and control clusters. These questionnaires will be translated into local language, and to be pilot tested before the start of definitive CLIP Trial, are as follows:

- Pregnancy registration questionnaire (Form 1 attached): will focus on resource utilization data, which will be useful to establish baseline resource utilization in the intervention and control clusters.

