- Regular community surveillance questionnaire (Form 2 attached): will focus on hospitalization of mother for pregnancy related illnesses, delivery and or newborn (after delivery) over the last 3 months. This information will be useful to quantify resource utilization (frequency of hospital visits, type of health facility), level of health facility, in-patient / out-patient care for delivery or pregnancy complications, length of stay, diagnostic tests, and therapeutic management. Also, information will be collected about mode of transport used, number of accompanying family members, days of missed wages, and information about negative externalities resulting in family-borne costs. Moreover, we will ask the respondents about out-of-pocket cost of illness for each health

resource utilized in the current pregnancy to determine unit cost estimation in the intervention and control clusters.

- Health facility patient admission chart review (Form 3 attached): will focus on the diagnostic and therapeutic interventions utilized by mother or newborn, which will be useful to quantify hospital resources utilization in the intervention and control clusters.

**2.5.2 *Review of hospital budget for health services:*** The unit cost of hospital services (diagnostics and maternal and newborn intervention) at the referral health centre will be obtained in the intervention and control clusters. The referral health facilities include both public and private health facilities, where the current CLIP Trial participants are being referred. The cost variables will focus laboratory investigations, maternal and newborn interventions as outlined in the form 3).

**2.5.3 *Review of district level cHCP program budget:*** The salaries of cHCP who are currently involved in the CLIP Trial will be determined through review of district level program budget. In addition, the transport expenses will be calculated for the extra visits of cHCP.

**2.5.4 *Review of site specific CLIP Trial budget:*** The unit cost estimates for CLIP Trial intervention package include the cost of blood pressure device, urine dipstick, oxygen saturation prop, cost of community engagement sessions, cost of training doctors, nurses, midwives, and community health workers will be determined from the trial budget for each site in the CLIP Trial.

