## 2.7 Participants' eligibility (Inclusion and exclusion criteria):

The pregnant women aged 15 – 49 years recruited in the CLIP Trial in both intervention and control clusters will be eligible to take part in the economic data collection (i.e., Form 1, Form 2 and Form 3) during the quarterly surveillance rounds. For qualitative assessments, only women who were identified at risk to a HDP in the pilot phase of the CLIP Trial, those willing to participate in 45-60 session will be eligible for participating in FGs. Likewise, husbands/father-in-law of those women (identified at risk to a HDP), those willing to participate in 45-60 session will be eligible for FGs. The CHCP handling the CLIP Trial package of intervention, the medical doctors at the referral health facilities where CLIP Trial participants are referred, and district health decision makers those willing to participate in 45-60 session will be eligible to participate in the FGs. Participants will be excluded, those who are not recruited in the primary CLIP Trial and or refuse to take part in the economics data collection procedures. The participants for qualitative assessments will be selected with the help of project staff, who are making home and health facility visits for CLIP Trial surveillance.

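### Appendix F applies Pakistan's quarterly surveys and pilot phase to Mozambique, so Form 2's 3-month look-back covers 3 of every 6 months there and 4 of 10 focus groups have no eligible participants as written

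*Protocol*

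**What the plan says.** **Scope.** Appendix F 2.2 states that "the economic evaluation of the CLIP Trial will take place in two countries (i.e., Pakistan, and Mozambique"). Section 2 of the appendix is one set of methods for both countries; India has its own section 3.

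**Survey timing.** Appendix F 2.5.1 says that the structured questionnaires "will be administered during the quarterly CLIP Trial surveillance in all intervention and control clusters". Form 2 "will focus on hospitalization of mother for pregnancy related illnesses, delivery and or newborn (after delivery) over the last 3 months". Main protocol section 2.10 is the only place that sets survey frequency country by country: "quarterly (Pakistan), 6-monthly (Nigeria and Mozambique), while in India, household surveys will continue prospectively using the MNH Registry".

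**Other sources of resource use.** In 2.5.1, Form 3 takes hospital tests and treatments from admission charts and has no look-back limit. The last item of Form 2 asks about out-of-pocket cost for resources used in the current pregnancy, again without the 3-month limit. Section 2.10 runs a chart audit of CEmOC admissions throughout the trial in every country except India.

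**Focus groups.** Appendix F 2.7 begins its rule with "For qualitative assessments, only women who were identified at risk to a HDP in the pilot phase of the CLIP Trial" and admits the husbands and fathers-in-law of those same women. Table 2 of the appendix plans 2 groups in each of 5 categories, 10 per site. Main protocol section 2.4 says: "There will be no Pilot phase in Mozambique".

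**The concern.** The appendix appears to have been written around Pakistan's calendar and then applied to both countries. Two of its rules do not fit Mozambique.

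The first is the look-back. A 3-month window at 6-monthly rounds leaves the earlier half of each interval unasked. Form 2 is the community source for admissions, visits, length of stay, transport and missed wages. The evaluation takes a societal perspective, so family costs are part of the target quantity. Package costs come from the trial budget in full, and deaths and morbidity are counted over the whole trial. Part of the care and family cost in Mozambique would be measured over a shorter period than the rest of the ratio, and the two countries would be measured over different windows without the plan saying so.

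The second is eligibility. The women's groups and the husbands'/fathers-in-law groups are the only family-side groups. They are meant to reveal cost drivers and implementation problems. A rule that admits only pilot-phase women excludes everyone in a country with no pilot.

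**Working it through.** **Inputs**

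- Form 2 look-back: 3 months (Appendix F 2.5.1).
- Survey interval: 3 months in Pakistan, 6 months in Mozambique (section 2.10).
- Focus groups: 2 in each of 5 categories (Appendix F, Table 2).
- Pilot phase in Mozambique: none (section 2.4).
- Assumption: events are spread evenly between rounds.

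**1. Form 2 coverage.** Coverage = min(1, look-back ÷ interval).

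- Pakistan: 3/3 = 100%, gap 0%.
- Mozambique: 3/6 = 50%, gap 50%.

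A simulation of evenly spread events with 6-monthly surveys and a 3-month window captured 50.2%, in agreement with the formula.

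**2. From Form 2 to all resource use.** Let s be the share of resource use that Form 3 chart review also captures. The uncounted share in Mozambique is (1 − 0.5) × (1 − s). The documents do not give s, so the full range is shown.

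| s | Uncounted share |
|---|---|
| 0 | 50% |
| 0.25 | 37.5% |
| 0.50 | 25% |
| 0.70 | 15% |
| 0.90 | 5% |
| 1 | 0% |

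Half is therefore the gap in Form 2's recall-limited items, and only the ceiling for resource use as a whole.

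**3. Which items are recall-limited.** The 3-month phrase is attached to hospitalisation, delivery and newborn care. Transport, accompanying relatives and missed wages come in a later sentence with no window stated. If the same window applies, they share the 50% gap and Form 3 does not recover them. If it does not apply, they escape it. Out-of-pocket cost is asked for the current pregnancy and is outside the gap.

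**4. Effect on the cost difference.** Suppose true use recorded only by Form 2 costs a per woman with intervention and b with control. Capturing half in each arm gives 0.5a − 0.5b = 0.5(a − b), so that component of the incremental cost is halved. If a = b, nothing changes. If a > b, the extra cost is understated. If a < b, the saving is understated. The documents give neither a nor b.

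**5. Focus groups.** The plan's own total is reproduced: 5 × 2 = 10. Groups that depend on pilot-phase women: 2 (women) + 2 (husbands/fathers-in-law) = 4, or 40%. The other 6 (community providers, facility doctors, district decision makers) are unaffected.

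**6. After correction.** With a 6-month window in Mozambique, coverage is 6/6 = 100%. With eligibility no longer tied to a pilot, all 10 of 10 groups have an eligible population.

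**The case against.** The strongest reply is that these are loose labels, not working rules. Section 2.10 has the survey teams collect births, deaths and care-seeking over the study period just past, which implies a look-back matched to each country's interval. The same section calls the surveys quarterly when describing a tablet application used in Nigeria, Mozambique and Pakistan together. Section 2.8 gives 9 follow-up surveys in 18 months, or one every 18/9 = 2 months, which matches no country's schedule. Forms 1 to 3 are described as attached but are not in the public text, so their wording in the field cannot be checked.

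Much of this stands. It makes it likely that Appendix F borrowed Pakistan's term, and it means that intent cannot be settled from the document. It does not remove the contradiction. Section 2.10 is the explicit country-by-country schedule, other sections tie quarterly rounds to Pakistan (2.6 and 2.9), and no section sets up separate quarterly rounds in Mozambique.

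On focus groups, section 2.15 (Economic analyses) and Appendix F 2.6 with its Table 2 describe the same groups with no pilot restriction. Section 2.1 also gives Mozambique an extended feasibility period for testing trial systems and tools. So three places permit the groups and one excludes them. The feasibility text does not say that women at risk were identified then, and the clause letting saturation set the number of groups does not change who is eligible. Section 2.7 is the eligibility rule, and it still needs correcting.

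A reader might also infer that about half of all resource use in Mozambique goes uncounted. The documents do not support that, because Form 3, the CEmOC audit and the current-pregnancy cost item have no 3-month limit.

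**Conclusion.** The point holds as an internal contradiction with a bounded consequence. Followed as written, Form 2 observes 3 of every 6 months in Mozambique, so up to 50% of its recall-limited data is missed, against 0% in Pakistan. This assumes evenly spread events and rounds held on the 6-monthly schedule. It covers hospitalisation, delivery and newborn care, and extends to transport and missed wages only if the same window applies to them. For all resource use the shortfall lies anywhere from 0% to 50%, depending on how much chart review recovers.

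It would be tempting to conclude that the Mozambican ICER is biased in a known direction. That cannot be shown. The appendix uses the same collection methods in both arms, so the error depends on how Form 2-only use differs between arms, and the documents do not give that difference. It does not cancel automatically either: section 2.9 expects the intervention to raise facility attendance and facility births.

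Under Appendix F 2.7 alone, 4 of 10 Mozambican focus groups have no eligible participants. It would go too far to say that the protocol as a whole rules them out.

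The economic evaluation is ancillary. Randomisation, the primary outcome, power and safety are untouched. The text should be corrected, but the trial does not turn on it.

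**What to change.** In Appendix F 2.5.1, define Form 2's window as the time since the last survey visit (3 months in Pakistan, 6 months in Mozambique). State that it covers the transport and missed-wage items as well. Replace the reference to quarterly surveillance with each country's surveillance cycle. This agrees with the look-back that section 2.10 already implies.

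In Appendix F 2.7, for Mozambique, define focus-group eligibility as women identified with HDP during the definitive trial, with their husbands or fathers-in-law. This brings 2.7 into line with section 2.15 and Appendix F 2.6.

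Both are wording changes and need no extra visits or staff. The cost is a 6-month recall period in Mozambique, which is likely to be less accurate than 3 months, so the difference in recall length should be stated when the two countries' cost results are reported.

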## **2.6 *Qualitative methods of data collection to inform design of cost modeling***

Focus group (FG) is commonly used method for data collection in qualitative research to gather group opinions. Specifically, the FGs in this study are aimed to better understand the contextual variations of intervention compliance, explore any additional resources utilized, and perceptions of benefits from community perspectives. The community perspectives will be obtained from women identified as hypertensive disorders of pregnancy, husbands / father-in-law of women identified at risk of HDP, cHCP, doctors at referral health facilities, and district health decision/policy makers. (Table 2)

The semi-structured guides have been developed for each focus group (see attached) to explore the community perspectives on the following priori themes:

- Theme I: Costs drivers and health resource utilization as result of the CLIP package of care.
- Theme II: Perceived benefits of the CLIP package of care and task-shifting to community health care providers.
- Theme III: Implementation challenges for the CLIP package of care.
- Theme IV: Strategies for knowledge translation of the CLIP package of care to the wider community.
- Theme V: Strategies for health policy advocacy and program scale-up of the CLIP package of care.

The FG guides will be translated into the local languages and will be pilot tested in a randomly selected intervention clusters before the actual data collection. The digital voice recorders and hand written notes will be used to record the participants' responses during

all FGs. The FG data will be transcribed into the local language, followed by translation into English. All the translations will be confirmed by researchers with back-translation of randomly selected data segments for quality control. We anticipate a total of 10 FGs inclusive of all groups at each site; however, the desired number of FGs will be determined by the data saturation.

Table 2: Number and distribution of FGs

| Number of Focus Groups with target population at each site |                                                      |                                 |                                           |                                          | Total |
|------------------------------------------------------------|------------------------------------------------------|---------------------------------|-------------------------------------------|------------------------------------------|-------|
| Women identified as HDP                                    | Husbands / father –in-law of women identified as HDP | Community health care providers | Doctors at the referral health facilities | District health decision / policy makers |       |
| 2                                                          | 2                                                    | 2                               | 2                                         | 2                                        | 10    |

